# A multifaceted strategy using mobile technology to assist rural primary healthcare doctors and frontline health workers in cardiovascular disease risk management: protocol for the SMARTHealth India cluster randomised controlled trial

**DOI:** 10.1186/1748-5908-8-137

**Published:** 2013-11-25

**Keywords:** Blood pressure, Capacity strengthening, Clinical decision support system, Healthcare workers, Physicians, India, Implementation

## Abstract

**Background:**

Blood Pressure related disease affected 118 million people in India in the year 2000; this figure will double by 2025. Around one in four adults in rural India have hypertension, and of those, only a minority are accessing appropriate care. Health systems in India face substantial challenges to meet these gaps in care, and innovative solutions are needed.

**Methods:**

We hypothesise that a multifaceted intervention involving capacity strengthening of primary healthcare doctors and non-physician healthcare workers through use of a mobile device-based clinical decision support system will result in improved blood pressure control for individuals at high risk of a cardiovascular disease event when compared with usual healthcare. This intervention will be implemented as a stepped wedge, cluster randomised controlled trial in 18 primary health centres and 54 villages in rural Andhra Pradesh involving adults aged ≥40 years at high cardiovascular disease event risk (approximately 15,000 people). Cardiovascular disease event risk will be calculated based on World Health Organisation/International Society of Hypertension’s region-specific risk charts. Cluster randomisation will occur at the level of the primary health centres. Outcome analyses will be conducted blinded to intervention allocation.

**Expected outcomes:**

The primary study outcome is the difference in the proportion of people meeting guideline-recommended blood pressure targets in the intervention period vs. the control period. Secondary outcomes include mean reduction in blood pressure levels; change in other cardiovascular disease risk factors, including body mass index, current smoking, reported healthy eating habits, and reported physical activity levels; self-reported use of blood pressure and other cardiovascular medicines; quality of life (using the EQ-5D); and cardiovascular disease events (using hospitalisation data). Trial outcomes will be accompanied by detailed process and economic evaluations.

**Significance:**

The findings are likely to inform policy on a scalable strategy to overcome entrenched inequities in access to effective healthcare for under-served populations in low and middle income country settings.

**Trial registration:**

Clinical Trial Registry India CTRI/2013/06/003753.

## Background

### Cardiovascular disease (CVD) burden in India

In India, the number of years of life lost due to CVD deaths among populations 35 to 64 years of age will increase from 9.2 million in 2000 to 17.9 million in 2030 – more life years lost than is projected for China, Russia, and the USA combined [1]. Elevated blood pressure (BP) is a major contributor to the increasing burden of CVD in India, estimated to be responsible for a million deaths annually [2]. India had an estimated 118 million people diagnosed with hypertension in 2000 with projections indicating a near doubling to 213 million by 2025 [3]. Around 16% of ischaemic heart disease, 21% of peripheral vascular disease, 24% of acute myocardial infarctions, and 29% of strokes in India are considered attributable to hypertension [4]. This disease burden is not confined to urban India. In rural areas, where 70% of the country’s population resides, high levels of hypertension and other CVD risk factors exist, with CVD already the leading cause of adult death in many such communities [5,6].

### Evidence-practice gaps in CVD prevention

Use of BP lowering treatments in rural India is limited, even where mandated low cost drugs are available in government formularies. Earlier studies done in rural communities in India have shown that few people with hypertension and/or CVD are appropriately managed [7,8]. In rural Andhra Pradesh, 27.0% of adults aged ≥30 years had hypertension with around one-half previously unidentified [6,8-10]. In these communities, 7.7% of adults had established CVD, and a further 8.1% had a 10-year CVD risk ≥ 30%. For those with CVD, 25% had non-optimal BP levels (systolic BP >140 mmHg). For those at high risk without known CVD, 95% had non-optimal BP levels. These rates were similarly experienced by men and women. Overall, only 39% of all high risk individuals with or without CVD have adequate BP control, indicating large evidence-practice gaps. In the context of limited resources, prioritising high-risk patients for BP lowering treatment is likely to be a highly cost-efficient approach and is consistent with Indian guideline recommendations.

### Workforce challenges

India’s health system faces great challenges in tackling a rapidly escalating burden of CVD. Key issues include lack of healthcare facilities, limited access to healthcare providers, and high out-of-pocket costs for consumers [11]. It is therefore imperative that innovative solutions are developed to address these issues. India’s three tier healthcare system provides nurse/midwife level primary healthcare at the sub-centre (population approximately 3,000 to 5,000), doctor-level care at the Primary Health Centre (PHC) (population approximately 20,000 to 30,000), and specialised care at the Community Healthcare Centres (population approximately 80,000 to 120,000). The PHC, which is usually led by one doctor, is expected to provide comprehensive primary healthcare for up to 30,000 residents. This leads to considerable strain on PHC resources potentially resulting in inadequate quality of care.

In this context, there is an urgent need for innovations in healthcare delivery. One promising strategy involves ‘task shifting,’ where front-line, non-physician health workers are delegated some of the tasks traditionally performed by physicians. In the setting of HIV/AIDS care, task-shifting has been shown to improve health outcomes and processes of care [12]. In India, there is some evidence that task shifting CVD risk assessment to non-physician health workers via a simple algorithm can increase the detection of CVD [13]. An example of front-line health workers in India is Accredited Social Health Activists (ASHAs), who are local female residents from the village. ASHAs have an average of ten years of formal education and are selected for this role by the village Panchayat (a village based self-governance system) and receive performance-based remuneration under India’s National Rural Health Mission program. On average, they work for two to three hours each day. Until now they have primarily been deployed to provide maternal and child health services via household visits. This suggests that this workforce can be trained to effectively identify people at high risk and refer them appropriately for medical care. In this study, the ASHA model is used as a platform for the integrated delivery of cardiovascular disease risk factor screening.

### Clinical decision support systems (CDSS)

In five systematic reviews on the effectiveness of CDSS, approximately two-thirds of controlled studies have demonstrated improvement in healthcare performance [14-19]. The vast majority of high quality trials, however, have been conducted in high income countries and have targeted physicians and other healthcare workers with high levels of training. The external validity of CDSS in Low and Middle Income Country (LMIC) settings is unclear [20]. One promising strategy to increase the uptake of CDSS in resource limited settings is through the use of mobile devices (mobile phones, smartphones and tablets). Given their increasing ubiquity, these devices represent one of the few hardware products available with the potential to transform the delivery of essential healthcare on a large scale. Research evidence to demonstrate this, however, is still relatively nascent. Despite the promise of an ‘m-health’ revolution in LMICs, a recent comprehensive review concluded that the current evidence for their effectiveness is fragmented and focused on intermediary outcomes such as cost savings and improved data quality [21].

### SMARTHealth – mobile decision support development

To help address these research gaps, we developed a novel comprehensive CDSS to facilitate Systematic Appraisal Referral and Treatment of CVD risk in rural India (SMARTHealth India). It has been designed for use by ASHAs and PHC doctors. A single screening and management algorithm was developed based on Indian and international guidelines. World Health Organisation/International Society of Hypertension (WHO/ISHs) region-specific risk charts are used to calculate a person’s ten-year absolute CVD event risk. For management recommendations, the Indian National Program for Prevention and Control of Cancer, Diabetes Cardiovascular and Stroke (NPCDCS) guidelines were programmed [22].

The algorithm was programmed into an application on a 7-inch tablet using Android 4.1 operating system. Both English and local language versions (Telugu) were developed. It was validated using a three-stage process based on our previous work [23]. Stage 1 was an iterative process where output from the algorithm was tested using de-identified data from patients in a previous rural Indian study and programming modifications were made. Stage 2 involved independently programming the algorithm into a statistical software package (SPSS v21.0, Armonk, NY). Primary de-identified healthcare data from 1,000 patients were imported into the CDSS and the SPSS program. For all output variables, the correlation (continuous variables) and agreement (categorical variables) between the two programs were assessed. A few minor coding errors in the CDSS were identified, rectified and re-tested until perfect correlation/agreement was achieved. Stage 3 involved user acceptance testing and field testing with doctors and ASHAs in 11 villages and 3 PHCs. Detailed analyses of the development and pilot phase will be published separately. Following the field testing, refinements were made to the system to make it system-ready for trial implementation.

## Research methods

### Study objectives

The SMARTHealth India study will test whether a CDSS will assist non-physician health workers and doctors in making evidence based management decisions to lower their patients’ CVD risks. The hypothesis is that a multifaceted intervention involving capacity strengthening of primary healthcare doctors and non-physician healthcare workers through use of a mobile device-based clinical decision support system will result in improved BP control for individuals at high CVD event risk when compared with usual healthcare.

### Study design

The intervention will be evaluated using a stepped-wedge cluster randomised, controlled trial (cRCT) of two years duration.

### Study population

A total of 18 PHCs (3 villages per PHC) in West Godavari District, Andhra Pradesh, will participate (see Statistical considerations below). Patients will be eligible to participate if they are residents of the study sites, are ≥40 years of age, are classified at high CVD risk and are indicated for BP lowering treatment based on WHO and NPCDCS guidelines.

High CVD risk is defined as the presence of any of the following:

1. Past history of CVD.

2. Estimated 10-year CVD risk ≥30%.

3. Estimated10-year CVD risk of 20% to 29% and a Systolic BP >140 mmHg.

Risk will be calculated using WHO/ISH algorithms for India.

### Randomisation

Cluster randomisation will occur at the level of the PHC. A total of 18 PHCs from West Godavari District in Andhra Pradesh will be selected. To be eligible, all PHCs must have at least one doctor regularly providing services, and all doctors must be willing to participate in the study. From the region serviced by each PHC, three villages will be randomly selected (54 villages in total). Six PHCs (18 villages) will be randomised to the intervention over 3 time intervals or steps (Table 1). Permuted block randomisation will be centrally performed at the George Institute in Hyderabad using a web-based form stratified by PHC size. Outcome analyses will be conducted blinded to intervention allocation.

**Table 1 T1:** Stepped-wedge randomisation of the participating villages to the intervention group in three time intervals or steps

	**Time interval**			
Number	Month 0–6	Month 7–12	Month 13–18	Month 19–24
6 PHCs (18 villages)	CONTROL	**INTERVENTION**	**INTERVENTION**	**INTERVENTION**
6 PHCs (18 villages)	CONTROL	CONTROL	**INTERVENTION**	**INTERVENTION**
6 PHCs (18 villages)	CONTROL	CONTROL	CONTROL	**INTERVENTION**

A stepped-wedge design will ensure that every participating PHC and village receives the intervention (for at least 6 months and an average of 12 months), while still allowing an unbiased evaluation of the effectiveness of the intervention compared to usual care.

### Intervention components

SMARTHealth allows health workers to collect consented patient information for screening and healthcare purposes and process this information based on the algorithm described above. The application then uploads this information for a doctor to review using OpenMRS – a secure, community-developed, open source, electronic medical record system platform. ASHAs can make electronic referrals to the PHC doctor, and doctors can notify the health worker via his/her tablet of the diagnosis and management plan. Figure 1 outlines the workflow and the key elements of the intervention package. The intervention comprises the following:

1. Equipment for ASHAs and PHC doctors to assess and manage CVD risk using the CDSS application in a 7-inch Smart Tablet. A backpack-sized kit, containing Smart Tablet, BP monitor, glucometer and other management resources will be provided.

2. The application will also support ASHAs to promote lifestyle advice for the determinants of high blood pressure and CVD, in particular physical activity, healthy diet and avoidance of tobacco and alcohol. There will be no out-of-pocket costs for participants accessing this service.

3. Training and resource support to ASHAs and PHC doctors. ASHAs will be provided with training in taking a patient history and measurement of BP and other CVD risk factors via the CDSS, provision of lifestyle advice to lower CVD risk; referral of high risk individuals and follow-up once seen by the doctor. Doctors will similarly be trained in use of the CDSS and additionally provided with training on pharmacological management.

4. A shared electronic record functionality using Open MRS and Sana to capture patient information via Smart Tablet and securely send data to a centralised server.

5. The doctors will use the electronic data transmitted by the ASHAs and interpret the decision support output for management of BP and other CVD risk factors. The decision support is based on current Indian national guidelines and will provide recommendations for BP lowering, lipid lowering, or anti‒platelet medications. The doctors will be advised to prescribe medications from these drug classes that are available on the essential medicine list in primary healthcare facilities to minimise out of pocket expenses.

6. A prompt system for follow-up of high risk individuals by ASHAs and doctors.

7. Both ASHAs and physicians have a permitted private practice allocation and will be remunerated accordingly. This is actively encouraged by district medical health officers and will ensure study participation will not divert the ASHA or the PHC doctor from their usual duties addressing other health priorities for the population.

**Figure 1 F1:**
[figure not shown]
Workflow and the key elements of the intervention package.

### Control arm

During control periods, access to healthcare will continue as per usual practice without the ASHAs and PHC doctors having access to the CDSS, associated tools, and the training and support package.

### Data collection

The study schema is outlined in Figure 2. Independent data collection will be conducted by trained household surveyors based on previous well-established and acceptable methods [6,8-10,13]. Collection will occur on five occasions for each village – at baseline, at each interim time-interval (*i.e*., each ‘step,’ see Table 1), and at the end of follow-up. This allows unbiased evaluation of effectiveness through comparison of ‘control periods’ (for each village, the period between baseline and pre-intervention) and ‘intervention periods’ (for each village, the period between pre-intervention and end of follow-up).

**Figure 2 F2:**
[figure not shown]
SMARTHealth study schema.

At baseline, a complete household survey (average of approximately 1,000 households per village) will be performed in each village. Trained field researchers will conduct interviews and make physical measurements using well-established methods [6]. In each household, every consenting adult aged ≥40 years of age will be assessed, and those at high risk of CVD will be identified, resulting in a census of all such individuals. Any individuals with extreme elevations of risk factors will be referred immediately for treatment. At each subsequent time point, data will be collected from a random independent sample of 15% of people identified at the baseline census as being at high risk (average of approximately 50 people per village). These data are for evaluation purposes only, and the ASHA and PHC doctors will not have access to this information.

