### Statistical considerations

A total of 18 PHC clusters (with 3 villages per cluster) progressively randomised by a third to the intervention (Table 1) will provide >90% power (2α = 0.05) to detect an absolute difference of 6% in the proportion of people with optimal BP levels. This translates to an increase in the proportion achieving optimal BP levels from 39% (based on our previous data) to 45% and a mean systolic BP difference of around 3 mmHg. These calculations maximise the study power afforded by a stepped-wedge design and assume an intraclass correlation coefficient (ICC) of 0.03 (more conservative than the ICC of 0.01 previously observed in this population) and 5 time-points for data collection. The mean village population is approximately 4,000, with one-third aged ≥40 years. Based on previous data from the region, approximately 23% of adults aged ≥40 years (approximately 300 individuals per village) are likely to be classified as being at high risk, with around 35% of these having established CVD [9]. Considering a conservative participation rate at each survey, a PHC cluster size of 150 patients per time point (approximately 50 per village) is anticipated on the basis of the above calculation. Methods based on mixed effects models as described by Hussey and Hughes will be used to analyse intervention effectiveness on primary and secondary outcomes, accounting for outcome variable type, potential time effects, clustering and stepped wedge design [24].

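### A 15% follow-up draw gives about 42 to 46 people per village before non-response, not the 50 (150 per PHC) used for the power statement

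*Protocol article*

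**What the plan says.** Three places in the protocol article bear on the follow-up sample size.

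- **Data collection.** Baseline is a full household census that lists all high-risk adults. Each later survey takes a "random independent sample of 15% of people identified at the baseline census as being at high risk (average of approximately 50 people per village".
- **Statistical considerations.** The size of that list is built up from "The mean village population is approximately 4,000, with one-third aged ≥40 years" and then "approximately 23% of adults aged ≥40 years (approximately 300 individuals per village) are likely to be classified as being at high risk". The power statement (>90%, two-sided 5%, 39% against 45%, ICC 0.03, five time points) uses the following size: "a PHC cluster size of 150 patients per time point (approximately 50 per village) is anticipated". The sentence that gives this size opens with "Considering a conservative participation rate at each survey", so 50 per village is presented as a number net of non-participation. No participation rate is given.
- **Abstract, Methods.** The trial is described as "involving adults aged ≥40 years at high cardiovascular disease event risk (approximately 15,000 people", in 54 villages.

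**The concern.** The sampling fraction, the size of the list and the expected yield are all printed, and they do not agree. A yield that already allows for non-participation cannot exceed the number drawn, but 50 per village is more than 15% of any list size the protocol gives. The list is also fixed at baseline and used for four further surveys over two years in a high-risk population, so deaths and moves can only reduce the yield.

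The number per PHC per survey is a direct input to the power calculation. The 15% is also an operating instruction: teams that follow it will, in an average village, miss the design size at every follow-up survey.

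**Working it through.** **Step 1. Yield of a 15% draw at full response.**

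| Source of list size | High-risk people per village | 15% per village | Per PHC (× 3) | Shortfall against 50 |
|---|---|---|---|---|
| Statistical considerations, stated | 300 | 45 | 135 | 10% |
| Statistical considerations, built up: 4,000 × 1/3 × 0.23 | 307 | 46 | 138 | 8% |
| Abstract: 15,000 / 54 | 278 | 41.7 | 125 | 17% |

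To draw 50 at 15% would need 50 / 0.15 = 333 listed people per village.

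**Step 2. Reproduce the stated power.** The model is the one the protocol names (Hussey and Hughes: fixed time effects, random cluster intercept), with a Wald test. There are I = 18 PHCs and T = 5 surveys, with six PHCs each on the patterns 00111, 00011 and 00001.

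- Total variance is 0.42 × 0.58 = 0.2436. Then τ² = 0.03 × 0.2436 = 0.007308 and σ² = 0.97 × 0.2436 = 0.236292. With m people per PHC per survey, s = σ²/m.
- Design constants: U = 36 (treated cells), W = 6² + 12² + 18² = 504, V = 6 × (9 + 4 + 1) = 84.
- Var = I·s·(s + Tτ²) / [(IU − W)·s + (U² + ITU − TW − IV)·τ²] = 18·s·(s + 0.03654) / [144·s + 504 × 0.007308].
- Power = Φ(0.06/SE − 1.96).

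At m = 150, s = 0.001575, SE = 0.01663, 0.06/SE = 3.61 and power is **95.0%**. The stated >90% is reproduced.

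**Step 3. Same calculation at the sizes from step 1.**

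- m = 138: 93.4%
- m = 135: SE 0.01751, 92.9%
- m = 125: SE 0.01818, 91.0%
- The smallest m giving 90% is 121. That is 121/135 = 90% response from a list of 300, or 121/125 = 97% from a list of 278. The protocol gives no response rate, so these are thresholds and not forecasts.

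**Step 4. Allow for the baseline census.** The 15% draw applies only after baseline. The baseline census covers about 3 × 300 = 900 people per PHC. The same model, by generalised least squares with unequal survey sizes, gives the following.

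| Per PHC at each follow-up | Census counted as first time point | Four follow-up surveys only |
|---|---|---|
| 135 | 96.5% | 90.3% |
| 125 | 95.3% | 88.1% |
| 115 (85% response from 300) | 93.9% | 85.5% |
| 108 (80% response from 300) | 92.6% | 83.3% |

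With the census counted, 90% is reached at about 97 per PHC per follow-up, which is 97/135 = 72% response from 300. With a list of 278 the census is 834 per PHC, the threshold is 98, and the response needed is 98/125 = 78%. With the four follow-up surveys alone, 134 per PHC are needed.

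**The case against.** The strongest reply is that the discrepancy is small and the power claim survives it. Every planning figure is marked as approximate, and 45 or 46 is not far from 50. The 278 comes from a rounded total in the abstract. The instruction to collect data from a 15% sample could mean 15% with completed data and not 15% approached. Even at equal survey sizes, power at full response is 91% to 93%. And baseline, which the protocol counts among its five occasions, is a census, so applying the reduced number to all five surveys understates the design.

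Much of this stands. A reader might infer that the stated >90% is lost at ordinary response rates, or that power should be restated in the 80s. The protocol does not support that. It gives no response rate, and the lower figures appear only under an assumed rate combined either with a baseline cut to follow-up size or with the census left out. It is also no answer to say that the census helps only if cluster effects are constant over time: every power figure from this model, including the reproduced 95.0%, makes that assumption.

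Rounding does not remove the inconsistency itself. If 15% means completed data, the yield is still 42 to 46. If it means people approached, the yield is lower. On neither reading is 50 a figure that already allows for participation.

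**Conclusion.** The sampling rule and the size behind the power statement cannot both hold as printed. The draw falls 8% to 17% short of 50 per village before any non-response. The >90% claim is not overturned, but its margin depends on two things the protocol leaves open: the participation rate, and whether the baseline census enters the primary comparison as the first time point. The minimum follow-up size for 90% power is about 121 per PHC with five equal surveys, about 97 with the census counted, and about 134 with the follow-up surveys alone.

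All figures assume ICC 0.03, 39% against 45%, a cluster effect constant over time and a normal approximation. This should be fixed; it is not a fatal flaw.

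**What to change.** Reconcile the abstract, Data collection and Statistical considerations in one of two ways, before the first follow-up sample is drawn.

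1. **Keep 15%.** State the participation rate assumed, restate the follow-up size per PHC as what 15% delivers (at most about 135), and recompute power, saying whether the baseline census is included. This costs wording and one recalculation.
2. **Keep 50 completed interviews per village.** Replace 15% by 50 / (300 × response rate): 16.7% at full response, 18.5% at 90%, about 20% at 85%, about 21% at 80%. The census list already exists, so only the draw changes. The cost is about 11% (16.7/15) to 40% (21/15) more people approached at each follow-up survey.

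In either case, use one figure for the number of high-risk people: 300 per village implies 300 × 54 = 16,200, against the abstract's 15,000.
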